## Abstract

**Background:**

Physical activity is associated with a lower risk of cognitive decline in older adults. However, past studies have demonstrated that older adults tend to relapse into inactivity after completing interventions. This ongoing study employs a randomized controlled trial design to assess the efficacy and efficiency of the KENKOJISEICHI local revitalization system for promoting daily outdoor behaviors to improve cognitive function in community-dwelling older adults with mild cognitive impairment (MCI).

**Methods/design:**

This 6-month randomized controlled trial will include 83 community-dwelling older adults aged 65 years or older with MCI. Participants will be randomized to the KENKOJISEICHI experimental group or an educational control group. The KENKOJISEICHI group will receive a 90-minute session twice per week that consists of social, intellectual, and physical activities involving outdoor behaviors intended to support cognitive function. Participants in the educational control group will attend two 120-minute educational classes during the 6-month trial period. Considering a 20–30% dropout rate, a sample size of 35 participants per group is required.

**Discussion:**

If the program successfully promotes long-term habitual outdoor behaviors, this will expand knowledge regarding how to support social, intellectual, and physical activities, as well as communication change, among the older population to provide them with cognitive benefits.

**Trial registration:**

University Hospital Medical Information Network (UMIN), Japan, UMIN000026479. Registered on 9 March 2017.

**Electronic supplementary material:**

The online version of this article (10.1186/s13063-018-2642-3) contains supplementary material, which is available to authorized users.

## Background

In mild cognitive impairment (MCI), several clinical and neuropsychological pathological features are present prior to the onset of overt Alzheimer’s disease [1]. Epidemiological data suggest that physical activity (PA) is associated with a lower risk of dementia [2], and many studies have identified the effects of exercise or PA on cognitive function in older adults with MCI [3–5]. Not surprisingly, there has been a sudden increase of interest in cognitive training and cognitive exercise interventions that can slow or reverse such changes or mitigate their detrimental effects [6].

Cognitive training and cognitive exercise interventions, involving guided practice of specific cognitive tasks, and cognitive stimulation programs, aimed at enhancing general cognitive functioning, have been offered to prevent or minimize the effects of cognitive aging. The effects of such cognitive interventions were investigated not only in healthy older adults but also in people with cognitive deterioration beyond normal age-dependent changes, such as people with MCI [6–8]. However, poor exercise adherence may be the most essential issue that hinders acquisition of health benefits and success of health promotion policies. Approximately 48% of older adults are reported to cease exercising within 6 months of initiation of an exercise program [9], subsequently leading to the loss of training effects [10].

Various studies have investigated factors that affect cognitive function and the development of dementia. In this context, the term social participation is used in a broad sense relating to society. Older adults with high levels of social participation are considered to have higher cognitive functioning than those with low levels of social participation [11–15]. In addition, social networks such as those related to work and volunteerism, as well as to friends and family, have been reported to exert a functional and protective effect with respect to dementia in older adults [14, 16]. Thus, it is possible that activity and cognitive function could be maintained by increasing social network involvement, such as with friends and family.

KENKOJISEICHI refers to a combination of health and self-employment, network development within one’s town, and a system of using neighborhood amenities such as stores, shops, cafes, supermarkets, libraries, community centers, and sports gyms in Takahama city, Aichi, Japan. We developed a structured program based on this concept, which combines physical, cognitive, and social activity promotion approaches with community resources for older adults. The program specifically focuses on helping participants to develop “continuous activities” based on enjoyment. These favorite activities include those that are physical, social, and intellectual, and involve participation in the community. Although such coordinated approaches have the potential to achieve substantial health promotion among the older population, they have not been adequately examined using randomized controlled trials. Therefore, the purpose of this study is to examine the effectiveness of the KENKOJISEICHI local revitalization system for promoting daily outdoor behaviors to improve cognitive function among community-dwelling older adults with MCI through a 6-month randomized controlled trial.

## Methods/design

### Design and setting

The study design is a randomized, single-blind, controlled trial. The 6-month-long study employs two groups: the KENKOJISEICHI course group and an educational control group. The study design and setting are shown in Fig. 1. This study will be conducted in Takahama city, Aichi, Japan. We have been conducting an observational study, including face-to-face interviews and measures of physical and cognitive function, in this community since 2015.

**Fig. 1 Fig1:**
[figure not shown]
Intervention schedule of enrollment, interventions, and assessments

This study was conducted in accordance with the guidelines proposed in the Declaration of Helsinki, and the study protocol was reviewed and approved by the research ethics committee of the National Center for Geriatrics and Gerontology (NCGG), Japan (approval no. 861-2). The protocol was registered with the UMIN Clinical Trials Registry (UMIN000026479). We held a meeting for all potential participants to explain the study purpose, measurements, and design, as well as to obtain written informed consent.

### Participants

A flow diagram of study participants is presented in Fig. 2. The study participants include community-dwelling older adults who were part of a subcohort of the National Center for Geriatrics and Gerontology–Study of Geriatrics Syndromes, conducted in Takahama from 2015 to 2016. The eligibility criteria were as follows: (1) aged 65 years or older; (2) not care-dependent or support-dependent on the Japanese long-term care insurance system; (3) independent in basic activities of daily living; (4) no diagnosis of Parkinson’s disease, dementia, or depression; (5) not restricted from exercising by a doctor; (6) no pacemaker; (7) not a KENKOJISEICHI administrator; (8) not going out every day according to the Life-Space Assessment (LSA; 1 km–10 km); (9) not employed; and (10) without MCI (amnestic MCI and nonamnestic MCI). Exclusion criteria were as follows: (1) no attendance at orientation, (2) consent not provided, (3) death or moving without notice, (4) not a participant in the preintervention assessment, (5) disability, and (6) severe health problems at baseline assessment. All of the participants read and signed the informed written consent form that was approved by the institutional review board for testing.

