## Discussion

Over one billion people, approximately 15% of the world’s population, are estimated to have some form of disability. These rates are increasing because of an expanding aging population and increases in chronic health conditions such as dementia [37]. Cognitive impairment may be associated with disability in older adults [38]. In this study, we will use a randomized controlled trial design to examine the effectiveness of the KENKOJISEICHI daily outdoor behaviors intervention in community-dwelling older adults with MCI. We hypothesize that participants in the KENKOJISEICHI group will maintain significantly higher cognition at the 6-month follow-up than the educational control group. Based on the transtheoretical model of outdoor behavior change, while cognitive training and cognitive exercise can shift people in the preparation and contemplation stages to the action stage, the outdoor behaviors support program is expected to guide participants to the maintenance stage, which is the essential stage for obtaining enduring health benefits from cognition.

Even during the outdoor behavior support period, older participants may return to an inactive lifestyle because of obstacles such as undesirable weather conditions, health issues, and family and community special events. The outdoor behaviors support program is designed to assist group activity, help them reflect upon issues arising, and help the group come up with its own ideas to overcome such issues. In addition to quantitative assessments of mediating social, psychological, and physiological factors, qualitative assessments focusing on self and group habitual activity will clarify how the outdoor behaviors support program will affect maintaining outdoor behaviors in participants’ daily lives.

If the outdoor behaviors support program successfully promotes maintenance of cognition and physical function, this will expand knowledge regarding supporting change in outdoor behaviors among the older population to obtain health benefits related to cognition. Moreover, the effective and less costly outdoor behaviors programs will be useful in creating a more meaningful and sustainable community-based network.

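### Eligibility criterion 10 is worded in reverse: it requires participants to be free of MCI, although the trial population is defined everywhere else as people who have it

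*Protocol article*

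**What the plan says.** The Participants section opens its list with "The eligibility criteria were as follows: (1) aged 65 years or older" and runs through ten numbered items. The tenth is "10) without MCI (amnestic MCI and nonamnestic MCI". A second list follows, opening with "Exclusion criteria were as follows: (1) no attendance at orientation, (2) consent not provided". It has six items, and none refers to MCI.

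The population is described in four other places:

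- Abstract, Background: the system is meant "to improve cognitive function in community-dwelling older adults with mild cognitive impairment (MCI".
- Abstract, Methods/design: the trial "will include 83 community-dwelling older adults aged 65 years or older with MCI".
- Background, final sentence (the study purpose): "to improve cognitive function among community-dwelling older adults with MCI through a 6-month randomized controlled trial".
- Discussion, first paragraph: the trial examines the "KENKOJISEICHI daily outdoor behaviors intervention in community-dwelling older adults with MCI".

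Trial status adds that participants had been recruited and that the intervention was under way when the manuscript was submitted.

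**The concern.** Eligibility criteria define the population to which a trial's result applies. Here the criterion that carries the disease definition points the wrong way. Anyone replicating the trial, judging whether its result applies to their own patients, or pooling it in a review of MCI interventions would take the population from this list. They would find people who have neither subtype of MCI. Criterion 4 also removes diagnosed dementia. The literal list therefore describes older people with neither MCI nor a dementia diagnosis, while the hypothesis and conclusions concern people with MCI.

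**Working it through.** No figure in the plan decides this point, so the check is a comparison of texts.

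**1. How the list works.** Items 1 to 9 make sense only as conditions to be satisfied: a minimum age of 65, independence in basic daily activities, no dementia diagnosis, no employment, and so on. Item 10 closes the same list. Read in the same way, a person is eligible only if MCI is absent.

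**2. Whether another reading rescues it.**

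| Reading of item 10 | Consequence | Tenable? |
|---|---|---|
| Condition to be met, like items 1–9 | Everyone with amnestic or nonamnestic MCI is ineligible | Follows from the text, but contradicts the stated population |
| Whole list is really a list of exclusions | Item 1 would exclude everyone aged 65 or older | No |
| Item 10 alone is a misplaced exclusion reason (people without MCI were screened out) | Agrees with the stated population | Plausible as the cause of the error, but the text does not say so: exclusions have their own list, and MCI is not in it |
| Item 10 is simply ignored | Nothing in items 1–9 or in the exclusion list selects on MCI, so people with and without it would both qualify | Does not yield the stated population |

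**3. Comparison with the stated population.** Four statements (two in the abstract, one each in the Background and Discussion) say that participants have MCI. None names people without MCI as the target. If the target is the set of people with MCI, and criterion 10 admits only people outside that set, the overlap is empty.

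**4. Effect on the numbers.** The inputs in the Sample size section are a change of 2.0 points, 80% power, 5% alpha error and 20–30% dropout, giving 35 per group. Criterion 10 is not among them, so correcting its wording leaves that stated calculation as it is.

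**The case against.** The strongest reply is that this is a slip of wording and that readers can see what was meant. Several points support it. Four consistent statements stand against one phrase. Naming both subtypes in brackets is natural for a required condition. The source cohort already had measures of cognitive function, so selecting on MCI was feasible. The criteria are reported in the past tense, after recruitment, so the list describes a selection already made.

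Most of this stands, and it limits what can be concluded. A reader might infer that the trial enrolled the wrong people, or that it cannot answer its question. The article supports neither inference: nothing in it shows that the rule was applied as worded. A reader might also put the problem as 0% of the target population eligible against 100% intended, but that only restates the contradiction and measures no effect. Nor can anything be said about what the participant flowchart reveals, since that figure was not available for this review; it may list the reasons for screening out and settle the matter.

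The reply does not remove the error. Criterion 10 is the only place where MCI status enters eligibility, the article states it explicitly, and it is reversed. This is not a detail that a condensed article leaves to a fuller protocol.

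**Conclusion.** Criterion 10 is wrong as written and must be reconciled with the stated population. Taken literally, it excludes every person the trial is about. This conclusion rests on the text alone: the inclusion list, the separate exclusion list and the four population statements. That the cause is a drafting slip is a judgement, likely but unconfirmed. The demonstrated harm is to the definition and reproducibility of the trial population. Harm to validity would follow only if people had actually been selected on the literal wording, and the article gives no evidence of that.

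**What to change.** 1. Reword criterion 10 so that MCI, amnestic or nonamnestic, is required, in line with the abstract and the study purpose. Deleting the item would not be enough, because no other criterion selects on MCI.
2. Confirm from the screening records that the randomised participants were selected on that basis. Recruitment was complete at submission, so rewording alone does not show which rule was applied.
3. If the check finds no one without MCI, a published one-line correction is sufficient. Only if it finds such participants, keep them in the intention-to-treat analysis already planned under Statistical analysis and add a sensitivity analysis limited to confirmed MCI.

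The cost is one corrected line and one check of existing records, with no new participants or procedures.

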**Fig. 2 Fig2:**
[figure not shown]
Flowchart of the study participants

### Sample size

The required sample size for this study was calculated using predictions of 6-month changes in NCGG Functional Assessment Tool (NCGG-FAT) results. On the basis of results of our previous work, we predicted that a change of 2.0 points would indicate a difference [17, 18]. To detect such a difference, with a power of 80% and alpha error of 5%, and considering a 20–30% dropout rate, a sample size of 35 participants per group was required.

### Randomization

After the baseline assessment, participants will be randomly assigned to the KENKOJISEICHI group or an educational control group. A researcher who is unaware of the aims of the study will perform the randomization procedure using computer-generated random numbers and will send the assignments to a researcher. Then, this researcher will notify the participants by mail. They will be told that they can stop the intervention at any time. They will also be asked to maintain their usual activities and to not participate in other research projects related to exercise or physical interventions.

### Planned trial interventions

#### KENKOJISEICHI group

The KENKOJISEICHI group will participate in classes focusing on 101 outdoor behaviors, including 28 physical activities, 29 intellectual activities, and 44 social activities; a small group gathering meeting will also be available. Locations that meet at least two of the following five examination requirements will be certified as healthy places: (1) places where KENKOJISEICHI group members can participate as they choose and can carry out activities with a purpose, (2) places where they can participate lightly, (3) places where people can interact with other people in the community, (4) places where the chosen activity can be performed, and (5) places where relaxation and relief can be realized. Nevertheless, a site that is used for political or religious activities or for the purpose of promoting these activities will not be recognized for KENKOUJISECHI purposes.

Social activities will be conducted in a community network and will include events such as traditional and health festivals, as well as visiting a cafeteria, drug store, shopping mall, temple, sightseeing spot, senior’s club, or variety store. Cognitive activities will include visiting a library, singing karaoke, playing the Japanese game Go, reminiscing (life review), arts and crafts, doing calligraphy, video impression, creating stamp art, and visiting an art museum. Physical activities will include Tai Chi, machine studio, indoor golf, walking, muscle strength training, stretch, hula dance, traditional dance, boccia, and social dance.

The intervention program consists of participating in social (16 times), intellectual (16 times), and physical activities (16 times). The forty-eight 90-minute sessions take place twice per week over 24 weeks and include a 15-minute condition check and stretching; 60 minutes of social activity, intellectual activity, or PA; and 15 minutes to write a report, provide impressions, and discuss the upcoming schedule. Participants will be divided into nine groups with two to four participants and two to three staff members in each group. The staff will manage the schedule, check health during participation, and prepare reports. This program focuses on improving outdoor behaviors and communication; therefore, it was designed to be simple and performed at any location in order to facilitate long-term adherence for all participants.

Participants will choose their next KENKOJISEICHI location by talking with the staff and through group-based activities (Table 1). The participants will record their impressions about the content of each day’s activity. Then, staff will write a brief activity report and note feedback from participants.

**Table 1 Tab1:** KENKOJISEICHI curriculum

	One time	Two time	Three time	Four time	Five time	Six time	Seven time	Eight time
A group	Social	Physical	Intellectual	Social	Physical	Intellectual	Social	Physical
B group	Physical	Intellectual	Social	Physical	Intellectual	Social	Physical	Intellectual
C group	Intellectual	Social	Physical	Intellectual	Social	Physical	Intellectual	Social
D group	Social	Physical	Intellectual	Social	Physical	Intellectual	Social	Physical
E group	Physical	Intellectual	Social	Physical	Intellectual	Social	Physical	Intellectual
F group	Intellectual	Social	Physical	Intellectual	Social	Physical	Intellectual	Social
G group	Social	Physical	Intellectual	Social	Physical	Intellectual	Social	Physical
H group	Physical	Intellectual	Social	Physical	Intellectual	Social	Physical	Intellectual
I group	Intellectual	Social	Physical	Intellectual	Social	Physical	Intellectual	Social

*Social* refers to social activity, *physical* refers to physical activity, and *intellectual* refers to intellectual activity

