### Statistical analysis

The data will be double-entered to enable validation. A coauthor, blinded to group allocation, will conduct preplanned statistical analyses for the primary and secondary outcomes. To ensure blinding, he will have no contact with the participants and use random numbers for group allocation. Intention-to-treat analysis will be applied to the outcome variables. Missing data will be imputed with the multiple imputation method [36]. Characteristics will be compared between groups using chi-square tests for categorical variables and the Mann-Whitney U test for continuous variables. Mixed-model analysis of variance will be carried out to test the effects of group, time, and the group × time interaction for all functional fitness tests. p Values < 0.05 will be considered statistically significant. All statistical analyses will be performed using IBM SPSS Statistics version 24.0 software (IBM, Armonk, NY, USA).

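### Only the intervention arm is delivered in nine small groups, and the stated model has no term for them, so if outcomes correlate within groups the test of the arm effect exceeds its 5% level

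*Protocol article*

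**What the plan says.** The Randomization section allocates individual participants after baseline. Under Planned trial interventions (KENKOJISEICHI group), the intervention arm alone is then "divided into nine groups with two to four participants and two to three staff members in each group". Table 1 letters these groups A to I and gives each its own sequence of activity types. There are 48 sessions of 90 minutes over 24 weeks. On where each session takes place, the text says: "Participants will choose their next KENKOJISEICHI location by talking with the staff and through group-based activities".

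The Educational control group section describes two classes over the six months and no small groups.

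The Statistical analysis section states: "Mixed-model analysis of variance will be carried out to test the effects of group, time", and adds the interaction of the two. Group here is the trial arm. No term for groups A to I or for staff is named. The section attaches this model to the functional fitness measures. No other outcome model is given, so it is an inference that the model also covers the primary outcome, the NCGG-FAT.

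The Sample size section works "with a power of 80% and alpha error of 5"%, and gives no ICC or design effect.

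**The concern.** Members of one small group share staff, places and each other's company for six months, and contact with others is part of what the programme sets out to change. It is plausible that their outcomes move together. Controls have no matching structure, so any such correlation enters one arm only.

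A model that omits the small groups treats intervention participants as independent given arm and time. With a positive within-group correlation, the mean of the intervention arm is more variable than that model assumes. The standard error of the arm effect is then too small, and the true type I error lies above 5%. A borderline positive result is the one most exposed.

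**Working it through.** **The plan's own figure.** The Sample size section says: "we predicted that a change of 2.0 points would indicate a difference", and "considering a 20–30% dropout rate, a sample size of 35 participants per group was required". No standard deviation is stated, so 35 cannot be reproduced. It can only be inverted (two-sided 5% assumed): SD = 2.0 / [(1.960 + 0.842) × √(2/n)].

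- 20% dropout: n = 35 × 0.8 = 28, implied SD about 2.67.
- 30% dropout: n = 35 × 0.7 = 24.5, implied SD about 2.50.
- No dropout: n = 35, implied SD about 2.99.

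The figure is attainable under independence, and nothing in it allows for clustering.

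**Inputs for the check.** Two to four per group and nine groups (KENKOJISEICHI group section); 5% level and 80% power (Sample size). Assumptions: equal arms, equal total variance in both arms, two-sided testing, and an ICC of 0.05, 0.10 or 0.20 for the outcome on which the arms are compared.

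**Formulas**, with m per group:

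- Design effect in the intervention arm: DE = 1 + (m − 1) × ICC.
- True over naive variance of the arm difference: V = (1 + DE)/2, since only one arm is clustered.
- Actual type I error of the naive test: 2 × [1 − Φ(1.96/√V)].
- Power of a test with the correct standard error, if 80% was planned under independence: Φ(2.802/√V − 1.96).

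Example with m = 4 and ICC 0.10: DE = 1 + 3 × 0.10 = 1.30; V = (1 + 1.30)/2 = 1.15; 1.96/√1.15 = 1.83; type I error 6.8%.

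| m | ICC | DE | V | Type I error | Power |
|---|---|---|---|---|---|
| 2 | 0.05 | 1.05 | 1.025 | 5.3% | 79% |
| 2 | 0.10 | 1.10 | 1.05 | 5.6% | 78% |
| 2 | 0.20 | 1.20 | 1.10 | 6.2% | 76% |
| 3 | 0.05 | 1.10 | 1.05 | 5.6% | 78% |
| 3 | 0.10 | 1.20 | 1.10 | 6.2% | 76% |
| 3 | 0.20 | 1.40 | 1.20 | 7.4% | 72% |
| 4 | 0.05 | 1.15 | 1.075 | 5.9% | 77% |
| 4 | 0.10 | 1.30 | 1.15 | 6.8% | 74% |
| 4 | 0.20 | 1.60 | 1.30 | 8.6% | 69% |

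At ICC 0.01 the type I error is 5.1% with three per group and 5.2% with four.

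**Simulation check** (100,000 runs per scenario, unadjusted t-test, nine clusters in one arm), for ICC 0.05, 0.10 and 0.20:

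- 35 per arm (eight groups of four, one of three): 5.7%, 6.7%, 8.3%.
- 28 evaluable per arm (one group of four, eight of three): 5.6%, 6.2%, 7.6%.

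Both agree with the formula.

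**Places against enrolment.** Nine groups of at most four hold 9 × 4 = 36. The Abstract has 83 participants. If allocation is 1:1, which is not stated, that is 41 or 42 in the intervention arm, or 41.5/9 = 4.6 per group, above the stated maximum.

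**The case against.** The strongest reply is that the Statistical analysis section lists the effects to be tested and need not list the random terms, and that a fuller plan, not shown, could include a small-group effect. That is possible. Still, the article describes a concrete delivery and a concrete model, and the two do not match. The point is raised against that stated model only.

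Other parts of the reply stand and limit the point:

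- The NCGG-FAT is taken individually, and nothing in the document shows that its change over six months clusters materially.
- Every group rotates through the same three activity types, 16 sessions of each, which would restrain differences between groups.
- Constant membership is suggested by the lettered groups in Table 1 but not stated, and staff are not said to belong to one group only.
- With nine groups of two to four, the between-group variance will be poorly estimated and may come out as zero.

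A reader might infer that the trial in effect has only nine intervention units. That holds only at ICC = 1, where four per group gives DE = 4 and 36/4 = 9. At ICC 0.10 the effective number is 36/1.30, about 28.

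A reader might also put about 4.6 people in each group, which gives simulated error rates of 6.0%, 7.1% and 9.5% for the three ICCs. Those rest on a 1:1 split that is not stated and on a group size above the stated maximum, so they should not lead.

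**Conclusion.** The point holds in conditional form. The stated model has no term for a grouping that exists in the intervention arm only, and for any positive within-group correlation its standard error for the arm effect is too small. For groups of three or four, the true variance of the arm difference is 5% to 30% larger than the naive one over ICCs of 0.05 to 0.20, and the actual type I error is about 5.6% to 8.6%. At ICC 0.01 there is no practical problem.

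This rests on an assumed ICC, equal arms with equal total variance, membership that is broadly stable, and the inference that the stated model also serves the primary outcome. The document does not support the flat statement that the p-values are too optimistic, because it gives no ICC.

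**What to change.** Fit the NCGG-FAT analysis as a partially nested model: a random effect for small group (A to I) in the intervention arm only, each control as a singleton, and small-sample degrees of freedom such as Satterthwaite. The random effect must act on the six-month outcome or on change. A group intercept shared by both assessments cancels out of the arm-by-time contrast and would correct nothing.

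Use the small group assigned at allocation for everyone randomized to the intervention, including those who never attend. Fit the model in each imputed data set, pool the results, and report the estimated ICC.

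Finalize the analysis code before the group labels are released, since labels that exist in one arm reveal allocation to the blinded analyst.

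State how nine groups of at most four accommodate the intervention share of the 83 participants, and give the allocation ratio.

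The labels already exist because Table 1 cannot be run without them, and delivery does not change. The cost is slightly wider intervals, an imprecise between-group variance from nine groups, and somewhat more work in combining the model with the imputation.
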